# Can regulatory T cells improve outcomes of sensitised patients after HLA-Ab incompatible renal transplantation: study protocol for the Phase IIa GAMECHANgER-1 trial

**DOI:** 10.1186/s12882-023-03157-7

**Published:** 2023-04-28

**Keywords:** Prospective study, Phase IIa, Regulatory T cells, Highly sensitised, Transplantation, Memory immune response, HLA, GMP, Polyclonal expansion

## Abstract

**Background:**

Kidney transplantation is the gold-standard treatment for patients with kidney failure. However, one-third of patients awaiting a kidney transplant are highly sensitized to human leukocyte antigens (HLA), resulting in an increased waiting time for a suitable kidney, more acute and chronic rejection, and a shorter graft survival compared to non-highly sensitised patients. Current standard immunosuppression protocols do not adequately suppress memory responses, and so alternative strategies are needed. Autologous polyclonally expanded regulatory T cells (Tregs) have been demonstrated to be safe in transplant settings and could be a potential alternative to modulate memory immune alloresponses.

**Methods:**

The aim of this trial is to determine whether adoptive transfer of autologous Tregs into HLA sensitised patients can suppress memory T and B cell responses against specific HLA antigens. This is a two-part, multi-centre, prospective clinical trial, comprising an observational phase (Part 1) aiming to identify patients with unregulated cellular memory responses to HLA (Pure HLA Proteins) followed by an interventional phase (Part 2). The first 9 patients identified as being eligible in Part 1 will undergo baseline immune monitoring for 2 months to inform statistical analysis of the primary endpoint. Part 2 is an adaptive, open labelled trial based on Simon’s two-stage design, with 21 patients receiving Good Manufacturing Practice (GMP)-grade polyclonally expanded Tregs to a dose of 5–10 × 106 cells/kg body weight. The primary EP is suppression of in vitro memory responses for 2 months post-infusion. 12 patients will receive treatment in stage 1 of Part 2, and 9 patients will receive treatment in stage 2 of Part 2 if ≥ 50% patients pass the primary EP in stage 1.

**Discussion:**

This is a prospective study aiming to identify patients with unregulated cellular memory responses to Pure HLA Proteins and determine baseline variation in these patterns of response. Part 2 will be an adaptive phase IIa clinical trial with 21 patients receiving a single infusion of GMP-grade polyclonally expanded Tregs in two stages. It remains to be demonstrated that modulating memory alloresponses clinically using Treg therapy is achievable.

**Trial registration:**

EudraCT Number: 2021–001,664-23.

REC Number: 21/SC/0253.

Trial registration number ISRCTN14582152.

**Supplementary Information:**

The online version contains supplementary material available at 10.1186/s12882-023-03157-7.

## Background

Around 30% of patients on the United Kingdom (UK) transplant waiting list are ‘highly sensitised’ (HS) (National Health Service Blood and Transplant (NHSBT) Annual Report Sept 2018), defined by the presence of Human Leucocytes Antigens (HLA) antibodies (Ab) capable of binding > 85% of the donor pool. As a group, these patients suffer two problems. First, they wait longer for an organ offer, as current standard of care is to only offer organs from donors to whom they have no Ab. To address the issue of waiting longer, the UK donor allocation scheme changed in late 2019 to give priority to HS patients. Disrupted by the COVID-19 pandemic, the full impact of this change on these patients is still not clear, but experience with similar changes in the USA indicates that a significant proportion, with the highest level of HLA antibodies, will not benefit from this [1]. UK Transplant Registry (UKTR) data (2020–21) suggests that after 5 years of waiting, 55% are transplanted, 11% have died, 10% become too frail for transplant, and 24% wait longer than 5 years. Therefore, this group of patients need urgent solutions. To help with offers, they can enter ‘delisting’ or ‘desensitisation’ programmes, where low levels of Ab are ignored (‘delisting’), or higher levels of Ab actively removed immediately prior to transplantation ('desensitisation'). Both these approaches widen the pool of organs available for offer and reduce waiting times and we have shown that patients opting for these programmes are not at higher risk of dying compared to waiting for a well-matched organ, which is the only other option for these patients without a living donor [2, 3]. These are risky options with poorer post-transplant outcome and are offered to selected patients by few centres; in the 5 years to March 2018, fewer than 100 cases were done in the UK. In the near future, novel therapies like Imlifidase [4, 5] or neonatal FcReceptors (FcR) antagonists [6] may offer more opportunity to widen the organ pool and reduce waiting times for this group of patients.

The second problem suffered by this group of patients occurs because the strategies to ignore or temporarily remove Ab allow transplantation to proceed, have no impact on memory alloreactive immune responses. Patients undergoing these procedures have higher rates of acute and chronic rejection, and require more immunosuppression, with all the resulting side effects including infection. Importantly, transplants in these patients have a shortened graft half-life [7, 8]. Five-year graft survival for HLA-incompatible transplants in the UK between 1 April 2021 and 31 March 2016 was 85.0%, compared to 93.2% for transplant from directed unrelated donors (NHSBT Annual Report 2020). We know that alloreactive memory T and B cells specific for donor HLA cause these problems in sensitised patients, despite the enhanced induction and maintenance immunosuppression these patients receive.

Regulatory T cells (CD4^+^CD25^+^Foxp3^+^) “Tregs” have unique immunosuppressive properties, essential in modulating immune responses and inflammation. In pre-clinical models, adoptive transfer of autologous Tregs can facilitate indefinite survival of allografts. This has fuelled an interest in their use in clinical transplantation. Our Good Manufacturing Product (GMP) facility has successfully isolated and expanded Tregs from 12 dialysis patients and demonstrated that they can be safely adoptively transferred back after transplantation (‘ONE study’) and Tregs expanded with the same protocol were used in 9 liver transplant patients ('ThRIL') [8–11]. To date, the focus of this approach has been to promote tolerance post-transplantation, but the aim of this study is to use autologous Tregs to suppress anti-HLA memory responses in sensitised patients awaiting transplantation. The rationale of this approached is based on both pre-clinical data [12] and observations from a study involving 43 patients with biopsy-proven chronic antibody mediated rejection (CAMR) [13, 14] where in donor-specific indirect alloreactive IFNgamma (IFNγ) ELISPOTs, ¾ of samples showed evidence of reactivity against donor antigens. In some patients, the presence of CD25^hi^ Tregs was associated with functional regulation of anti-donor responses by B cells, which reverted to a conventional antigen-presentation role when the Tregs were depleted. These findings have been validated more recently in the 62 patients recruited to the RituxICAN-C4 trial [15]. Thus, Tregs in some patients with CAMR appeared to be modulating anti-donor reactivity, potentially via an effect on antigen-specific B cells and/or T cells. Recently, we associated these patterns of in vitro regulation by CD25^+^ cells, with improved prognosis after 3-year follow-up [14].

In preliminary analyses, we have documented similar patterns in sensitised dialysis patients who have rejected a previous transplant, suggesting that even after the cessation of immunosuppression, patients maintain the ability to regulate responses to specific donor antigens, even though they have made an Ab to that antigen. All these data suggest that augmentation of Treg numbers in patients with HLA Ab may potentially inhibit T &B cell memory responses via interactions with either T or B cells. In support of this, Tregs infused into liver transplant patients in the ThRIL study (at doses lower than we are planning here), have been shown to suppress in vitro ‘direct’ anti-donor responses [9]. Therefore, our hypothesis is that augmentation of Treg numbers in sensitised patients will suppress T cell anti-HLA memory responses for 2 months at least, a period of time that we assess will be clinically useful. The stability or variability of anti-HLA responses over time in patients with end stage renal failure (ESRF) remains unknown, as no-one has studied serial antigen-specific responses in these patients. Important questions relate to whether suppression by Tregs varies spontaneously, and whether it is possible to identify differences induced by Tregs from this background variation.

In this trial, after having identified 21 patients with reactivity against soluble HLA (sHLA) from Pure Protein® (Part 1), we will conduct an adaptive Phase IIa clinical trial (Part 2). The first 9 patients identified as being eligible for Part 2 of the study will undergo baseline immune monitoring for 2 months to inform statistical analysis of primary endpoint. In Part 2 of the study, 12 patients will receive a single infusion of GMP grade polyclonally expanded Tregs in stage 1. After assessing the responses of these for futility/efficacy, we will then administer Tregs to the remaining 9 patients in stage 2 if ≥ 6 patients pass the primary EP in stage 1. The primary EP is suppression of in vitro memory responses for 2 months post-infusion.

## Methods/ design

### Study design

The trial flow chart is presented in Fig. 1. The study has two parts: Part 1 will be observational to record functional responses by patient peripheral blood mononuclear cells (PBMC) to sHLA from Pure HLA Proteins ® in FluoroSpot assays. The pattern of these responses forms the basis of eligibility to Part 2. The first 9 patients identified as being eligible will undergo baseline immune monitoring for 2 months to inform statistical analysis of primary endpoint. Part 2 is an adaptive, multi-centre, open-label, one-armed, phase IIa clinical trial, based on Simon’s two stage design, with 12 patients treated in stage 1 and 9 treated in stage 2.

**Fig. 1 Fig1:**
[figure not shown]
Trial Flow chart Part 1 Observational study: Identification of patients eligible for Part 2, based on pattern of IFNg/IL-17 reactivity on FluoroSpot assay. Some patients may have already had these assays performed in 2020 as part of an observational study (REC ref 16/WM/0370). Additional patients (up to n = 100) will be recruited and have blood withdrawn for testing to determine HLA-specific patterns of responsiveness in FluoroSpot assays, to identify those eligible for Treg therapy in Part 2, and to determine the size of the population for our proposed follow-on trial (beyond this study). All patients with either positive IL-17 or IFN gamma anti-HLA reactivity without evidence of regulation by CD25 + cells will be eligible to enter Part 2. The first 9 patients identified as being eligible, from any site, will undergo baseline immune monitoring for two months to inform statistical analysis of primary endpoint. If < 21 patients with Fluorospot patterns eligible for inclusion in Part 2 are identified, the study will terminate early. Part 2 Interventional Study: This is a two stage, adaptive, open labelled, trial based on Simon’s two stage design, with 12 patients treated in Part 2 Stage 1 and 9 treated in Part 2 Stage 2. Because of an expected high withdrawal rate, all patients recruited to Part 1 will consent to inclusion in Part 2. If more than 21 eligible patients are identified, the statisticians will draw up an algorithm at the end of milestone 1 to determine which patients are included in Part 2, to ensure that eligible patients from each of the three sites are included in a ratio proportionate to the number found eligible from each site. For instance, if after 75 patients have been analysed in Part 1, the number found eligible at each site is 15 (site 1), 10 (site 2) and 10 (site 3), then 9 from site 1 will be included, and 6 each from sites 2 and 3. The order of Treg dosing will be determined by the order in which eligibility for Part 2 was determined. Treg dosing: The exact number in Part 2 Stage 2 who receive Tregs will be determined by the results from Part 2 Stage 1, according to Simon’s 2 stage design. If fewer than 2 of the 12 in stage 1 reach primary endpoint (suppression of anti-HLA responses for at least two months post treatment), the trial will be stopped, concluding that Treg therapy has no efficacy. If 6 or more of the 12 in group 1 reach primary endpoint, we will proceed with dosing all 9 in stage 2. In the event that 3, 4 or 5 of the 12 patients in stage 1 respond, the estimates of efficacy are below our hoped for 50% but are not so low as to be regarded as evidence of futility. We will therefore pause the trial and re-estimate the number of patients that we need to recruit, after discussion with the funders. We anticipate withdrawals from both Part 1 and Part 2, for various reasons including transplantation, and so will likely enrol more than 21 patients to Part2

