### Statistical considerations and analysis

#### Sample Size calculation

Based on our previous experience of numbers of patients presenting anti-donor reactivity without evidence of suppression by CD25^+^ T cells, we have calculated that 100 patients will need to be recruited for Part 1. This number is based on availability of the clinical population in the study sites which is feasible in the study timeframe. For Part 2, Simon’s two-stage design will be used for the trial, with α = 0.05 and 1-β = 90%. Clinical consensus amongst the expert team is that if fewer than 20% meet the primary endpoint there is no merit in further investigating Tregs, whereas if ≥ 50% respond to Tregs further investigation will be merited. Based on these parameters, 21 patients are required, all of whom will be monitored for at least 2 months post-treatment to meet the data collection for the primary endpoint. Of these 21 patients, 12 will be allocated to stage 1 and 9 to stage 2, based on the order of recruitment. At the end of stage 1, data will be assessed for futility using stopping rules based on the clinical consensus: ≥ 6 patients meeting the primary endpoint, stage 2 will commence; ≤ 2 patients meeting the primary endpoint, the trial will stop; 3–5 patients meeting the primary endpoint, the trial will pause for the sample size to be re-estimated after discussion with the funder.

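### Fig. 1 stops below 2 of 12 responders and the Methods stop at 2 or fewer, so 2 of 12, the likeliest count at the 20% null rate, has no agreed action

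*Protocol article*

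**What the plan says.** The rule for moving from stage 1 to stage 2 of Part 2 appears in full in two places in the protocol article.

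- **Fig. 1 legend.** The trial stops for lack of efficacy "If fewer than 2 of the 12 in stage 1 reach primary endpoint". It pauses for a new sample size estimate "In the event that 3, 4 or 5 of the 12 patients in stage 1 respond". It proceeds to dose all 9 stage 2 patients at 6 or more.
- **Sample Size calculation.** "≤ 2 patients meeting the primary endpoint, the trial will stop"; 3 to 5 leads to a pause, and 6 or more starts stage 2.

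The same section gives the design inputs: a Simon two-stage design with alpha 0.05 and 90% power; a null rate of 20%, since "if fewer than 20% meet the primary endpoint there is no merit in further investigating Tregs"; a target rate of 50%, at or above which the plan would go on; and the result, "Based on these parameters, 21 patients are required", of whom "12 will be allocated to stage 1 and 9 to stage 2".

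**The concern.** The pause and proceed zones agree in both places; only the stop boundary differs. With exactly 2 responders the Methods say stop. The legend excludes 2 from its stop rule and starts its pause zone at 3, so it says nothing.

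This is the trial's only stated futility threshold, and the trial is open-label. If stage 1 ends with 2 responders, anyone working from the legend would have to choose the action after seeing the result, which is what a pre-specified boundary is meant to prevent. At stake is whether up to 9 more patients undergo leukapheresis and cell infusion after a result that the design counts as futile.

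**Working it through.** **Inputs** (all from Sample Size calculation unless noted): null rate p0 = 0.20; target rate p1 = 0.50; alpha = 0.05, taken as one-sided as is usual for a Simon design; power 90%; n1 = 12, n2 = 9, N = 21. Stop rules: X ≤ 2 (Methods) and X ≤ 1 (Fig. 1 legend).

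**Step 1. Reproduce the plan's sample size.** Exact enumeration of all two-stage designs with alpha ≤ 0.05 and power ≥ 0.90 gives the minimax design n1 = 12, stop if X ≤ 2, N = 21, declare activity if more than 7 of 21 respond. Its exact alpha is 0.0421 and its power 0.9010. The plan's 21 and its 12 + 9 split are reproduced exactly, and the stage 1 boundary that belongs to them is 2 or fewer.

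**Step 2. Stage 1 probabilities at p0.** P(X = x) = C(12, x) × 0.2^x × 0.8^(12−x).

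- P(0) = 0.8^12 = 0.0687
- P(1) = 12 × 0.2 × 0.8^11 = 0.2062
- P(2) = 66 × 0.04 × 0.8^10 = 0.2835
- P(3) = 0.2362; P(4) = 0.1329; P(5) = 0.0532; P(6 or more) = 0.0194

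The largest is P(2). Two is the mode whenever 13p lies between 2 and 3, that is for null rates from 15.4% to 23.1%.

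**Step 3. Early stopping at p0.**

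- Methods: P(X ≤ 2) = 0.0687 + 0.2062 + 0.2835 = 0.558
- Legend, if the trial does not stop at 2: P(X ≤ 1) = 0.0687 + 0.2062 = 0.275

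The difference is P(2), about 28 percentage points.

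**Step 4. Effect on the underlying Simon design.** This step assumes that every result above the stop boundary continues to 21 and that the final boundary is the minimax value of 7, which the article does not state. Expected N = 12 + 9 × (1 − probability of early stopping).

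| Stage 1 stop rule | Early stop at p0 | Expected N at p0 | Alpha | Power |
|---|---|---|---|---|
| 2 or fewer | 0.558 | 12 + 9 × 0.442 = 16.0 | 0.0421 | 0.9010 |
| fewer than 2 | 0.275 | 12 + 9 × 0.725 = 18.5 | 0.0430 | 0.9051 |

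Alpha and power barely move because a trial with 2 of 12 would need at least 6 of the last 9 to succeed. At p1 = 0.50, P(2 of 12) = 0.0161 and P(at least 6 of 9) = 130/512 = 0.254, so the gain in power is 0.0161 × 0.254 = 0.004.

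**Step 5. Which wording fits the rest of the plan.** Two of 12 is 16.7%, below the 20% no-merit threshold; 3 of 12 is 25%, above it. The legend itself describes 3 to 5 responders as too many to count as futility, which places the futility zone directly below 3. Both observations agree with Step 1.

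**The case against.** The best defence is that the two places do not give opposite orders at 2 of 12. The Methods give a complete rule and the legend merely leaves a gap, which a reader would fill from the Methods. On that reading early stopping stays at 55.8% and nothing is lost. That much is right: the halving to 27.5% is a worst case that arises only if the trial carries on at 2.

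The expected sample sizes in Step 4 are also not this trial's own, because at 3 to 5 responders both places pause and re-estimate. Only 6 or more goes straight to stage 2, with probability 1.9% at p0. The looser boundary would still meet the 5% and 90% targets, so the error rates alone do not rule it out. The article does not name the minimax design or state the final boundary, and it attributes the stopping rules to clinical consensus. Finally, the full protocol and any committee charter are not shown and may be correct.

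These points limit the size of the harm. They do not remove the disagreement: two legible, current statements of the same go/no-go threshold differ, and they differ at the likeliest null result. The stage 1 probabilities in Steps 2 and 3 do not depend on the final boundary or on what happens at 3 to 5.

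**Conclusion.** The concern holds. The legend's stop boundary contradicts the Methods and leaves 2 of 12 without an action. That result has probability 28.3% if the true response rate is 20%, and 1.6% if it is 50%. Read literally, with no stop at 2, the legend cuts the chance of early stopping at the null rate from 55.8% to 27.5%. The cost in alpha (4.2% against 4.3%) and power (90.1% against 90.5%) is negligible, given continuation to 21 and a final boundary of 7. The stated parameters, the 20% threshold and the legend's own remark on 3 to 5 responders all point to 2 or fewer as the intended boundary. It must be corrected, because a futility threshold has to be unambiguous before stage 1 results are seen.

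**What to change.** Change the Fig. 1 legend to stop at 2 or fewer of the 12 (equivalently, fewer than 3), so that it matches the Sample Size calculation section and the Simon design behind the 12 + 9 split. Use one decision table wherever the rule appears: 0 to 2 stop, 3 to 5 pause and re-estimate, 6 or more proceed.

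Check the full protocol and the data monitoring committee's charter for the legend's wording and correct it there if present. In the article the cost is one line; sample size, assessments and analysis are unaffected. The correction should be in place before stage 1 responses are reviewed.

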
### Study participants

Adults with kidney failure awaiting transplantation will be identified from the local kidney transplant waiting list at 3 UK hospitals. The direct care team will approach potential participants and patient information leaflets, describing parts 1 and 2 handed out, emailed or posted to the patient after permission to do so has been obtained. Participants will be offered the opportunity to discuss the trial with the recruiting team. Patients will be asked to provide written consent to inclusion in both Part 1 and Part 2 of the study. Following consent, full eligibility criteria will be reviewed.

### Inclusion criteria

The inclusion criteria for Part 1 are listed as follows:1) Adult (≥ 18yrs) dialysis on the deceased donor renal transplant waiting list with HLA Ab and a Calculated Reaction Frequency (CRF) ≥ 50%2) HLA Ab specificities corresponding to available sHLA from Pure Protein.3) Able to give written informed consent.4) All females of childbearing potential (which is strictly defined in the protocol) and males whose partner is of childbearing potential must be willing to use highly effective methods of contraception if going into Part 2 and continue to use to the end of phase 2 follow-up. Highly effective methods of contraception are strictly defined in the protocol.

Additional inclusion criteria will be confirmed before Part 2 of the study:1) Dual FluoroSpot assay result to sHLA from Pure HLA Proteins® that indicates anti-donor reactivity without evidence of suppression by CD25^+^ T cells in Part 1 (spot count increase, after depletion of CD25 + cells of < 20%).2) Female participants of childbearing potential and male participants whose partner is of childbearing potential must be willing to reconfirm that they or their partner use highly effective contraception during Part 2 of the trial.

### Exclusion criteria

The exclusion criteria for Part 1 are defined as follows:1) Living donor kidney transplant planned.2) Listed as recipient of multi-organ transplants (i.e. combined kidney and pancreas).3) Known Human Immunodeficiency virus (HIV) + or previous Hepatitis C Virus (HCV) or Hepatitis B Virus (HBV). If no HIV, HCV or HBV tests within 5 years, these will be performed post-consent.4) Patient involved in other clinical trials of investigational medicinal products (IMPs).5) Active infection or history of recurrent infection. Recurrent infection defined as more than 2 confirmed infections requiring either antibiotics, antivirals, antifungals or hospitalisation in 6 months prior to consent.6) Female patients of childbearing potential with a positive pregnancy test at enrolment.7) Female patients who are breastfeeding.8) Hypersensitivity to IMP or to any of the excipients.9) Known contraindication to the protocol-specified treatments or procedures.10) Severe liver impairment, defined as ≥ Grade 3 or severely elevated ALT, AST or total bilirubin, on bloods done within the last 3 months.11) Electrocardiogram (ECG) abnormalities suggesting active myocardial ischaemia or (potentially) malignant ventricular arrhythmia: ECG to have been performed within the last 3 months.12) Patients, who in the opinion of the PI, have a medical condition, or other relevant psychological, familial or social factor that may jeopardise their health, compliance, or influence the trial integrity in any way.

Exclusion criteria 1 and 4–12 will be re-checked at a screening visit prior to patient entering Part 2.

